### Interventions

TKA regimens designed according to TKM clinical experts will be used in this trial for alleviating hot flushes and vasomotor symptoms by balancing yin and yang in the participant. These regimens were also used in two previous studies [25], one of which is unpublished and mentioned above. The TKM doctors who conduct the treatments have practiced for at least 3 years in the clinic; they belong to each clinical center spread among different provinces in South Korea.

Participants will be randomly assigned to either the acupuncture treatment plus usual care group or the usual care alone group. The acupuncture treatment plus usual care group will receive acupuncture 3 times/week, for a total of 12 sessions. Six acupuncture points (ST36, SP6, LI4, PC6, HT7, HT8) will be inserted bilaterally in the four peripheral extremes and one point (CV4) will be inserted unilaterally in the lower abdominal region. TKM doctors will manually manipulate the acupuncture needles with de-qi sensation and maintain the needles for 20 minutes with intermittent manual stimulation. Infrared irradiation will be used to warm the lower abdomen during the 20 minutes of acupuncture treatment, as it is performed in conjunction with acupuncture, generally.

TKM doctors will use sterile, disposable needles with a length of 40 mm and a diameter of 0.25 mm (Dongbang Acupuncture Inc, Korea). They will be inserted to a depth of 3–15 mm, according to the points selected.

Participants who will be allocated to usual care alone group will receive no acupuncture treatments throughout the 4 weeks. They will record their hot flush symptoms in a daily diary. After four weeks, if participants elect to try the acupuncture treatment, the same treatment will be provided.

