**Methods:**

This study consists of a multi-center randomized controlled trial with 2 parallel arms. Participants included in the study will meet the following criteria: 1) a documented daily average hot flush score ≥ 10 for one week prior to the screening visit 2) not taking HRT and other pharmaceutical therapies which might affect hot flushes or other vasomotor symptoms.

While maintaining usual care, the treatment group will receive acupuncture 3 times a week, for a total of 12 sessions over 4 weeks. The control group will receive usual care alone during the same period. Post-treatment follow-up will be performed one month after completing 12 sessions of acupuncture.

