**Discussion:**

This trial will provide evidence for the effectiveness of acupuncture as a treatment for hot flushes. The primary endpoint in both groups is a change in hot flush score from baseline to week 4 and/or week 8. As the secondary endpoint, we will employ the Menopause Rating Scale (MRS), a health-related quality of life questionnaire. Further analysis will examine the frequency, severity and difference in symptoms for daytime vs. nighttime hot flushes, sub-domain analysis of MRS, and participants' expectations of acupuncture treatment.

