### Study outcome

The primary outcome measure is the hot flush score, produced by multiplying severity and frequency of hot flushes during a 24-hour period in a daily diary, which demonstrates validity and reliability in measuring hot flush activities [27]. Participants will be asked to record the number and severity of daily hot flushes during the entirety of the study period. Participants in both groups will also be routinely encouraged to fill out the diary by periodic short message service (SMS) and phone-call reminder both in order to avoid the selective loss to follow up, that is, selection bias and to prevent the indolence of writing daily diaries which are associated with participant knowledge-related bias in this unblinded trial. We will employ the slightly modified severity rating scale (0:none, 1:mild, 2:moderate, 3:severe, 4:very severe) suggested in the studies of Sloan et al. [27].

We will examine the reduction in hot flushes over a 24-hour period, as well as daytime and nighttime separately for sub-analytic purpose to check whether acupuncture has different effects on daytime versus nighttime hot flushes.

The secondary outcome measure is the Menopause Rating Scale (MRS) to assess other vasomotor symptoms. MRS is a highly qualified self-administered questionnaire for assessment of menopausal symptoms [37]. It contains 11 questions divided into 3 categories: psychological, somatic and urogenital.

We will also estimate the expectations of participants by using the credibility and expectancy questionnaire, aiming to determine whether expectations make a difference to outcome [38,39]. In order to assess expectations without potential influences by participants' knowledge of allocation results, a questionnaire will be administered to eligible women before notification of assignments. Data collection schedule is detailed in table 2.

**Table 2 T2:** Data Collection Schedule

Measures	Screening	Baseline Randomization				End		Follow-up
Week number	-1	0	1	2	3	4	6	8

Sociodemographic characteristics	O							
Hot flush diary	O	O	O	O	O	O	O	O
Credibility and Expectancy questionnaire		O						
MRS		O		O		O	O	O
Medical history	O							
Physical activity	O							
Smoking/Alcohol	O							
Pharmaceutical therapies (OTC and prescribed drugs)	O	O	O	O	O	O		O
Herb medications	O	O	O	O	O	O		O
Adverse effects			O	O	O	O		
FSH, Estradiol	O							
TSH, Free T4	O							

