### Statistical methods and sample size

Analyses will be performed for two populations: 1) an intention-to-treat population consisting of all randomized participants with at least one measurable outcome report following acupuncture treatment (missing data will be replaced with last observation values); 2) a per protocol population including only participants without major protocol deviations. All data will be analyzed descriptively. All main analyses will be based on the intention-to-treat population. For primary and secondary outcome measures, the mean differences from baseline values to the end of treatment will be compared using two-sample t-test or Wilcoxon rank sum test. A trend test will also be performed using repeated measures analysis of variance. We adjusted for possible confounders using criteria of statistical significance.

All adverse events reported during the study will be included in the charts; then incidences of adverse events will be calculated. The percentage of the subjects with adverse events in each group will be calculated and compared with the chi-squared test or Fisher's exact test value.

Statistical analyses will be performed using the SAS statistical package program (ver. 9.1.3) and the level of significance will be established at α < 0.05. In calculating the sample size, we assumed a power of 90% and α value of 5%, in order to detect a hot flush score difference of 15.34 with a standard deviation of 26.5 drawn by two previous studies in Korea [24,41]. Therefore the acupuncture plus usual care and usual care alone group (2:1 allocation) will include 120 and 60 participants, respectively, allowing for a 20% withdrawal rate. This implies a sample size of 45 for each center, with 30 participants per acupuncture treatment plus usual care group and 15 per usual care alone group.

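### Week 8 is allowed as a primary time point although controls may start the same acupuncture after week 4, so a week-8 group difference would not be against usual care alone

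*Protocol article*

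**What the plan says.** - **Control condition (Interventions).** Up to week 4 the contrast is clean: "Participants who will be allocated to usual care alone group will receive no acupuncture treatments throughout the 4 weeks." After that, acupuncture is optional for controls: "After four weeks, if participants elect to try the acupuncture treatment, the same treatment will be provided."
- **Primary endpoint (Abstract, Discussion).** "The primary endpoint in both groups is a change in hot flush score from baseline to week 4 and/or week 8."
- **Follow-up (Abstract, Methods).** "Post-treatment follow-up will be performed one month after completing 12 sessions of acupuncture", which places it at about week 8.
- **Data collection (Study outcome and Table 2).** "Participants will be asked to record the number and severity of daily hot flushes during the entirety of the study period." Table 2 labels week 4 as the end and marks the diary and the MRS at weeks 6 and 8, without separating the arms.
- **Analysis (Statistical methods and sample size).** For primary and secondary outcomes, "the mean differences from baseline values to the end of treatment will be compared using two-sample t-test or Wilcoxon rank sum test." The section adds: "A trend test will also be performed using repeated measures analysis of variance." It does not name the visits in that analysis.

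The article does not say how control data are handled once a control has started acupuncture.

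**The concern.** The stated aim is to compare acupuncture plus usual care with usual care alone. That comparison exists by design for four weeks. The regimen is 12 sessions at three per week, so a control who starts promptly after week 4 is being treated through roughly weeks 4 to 8, the same window as the later measurements.

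The Abstract still allows week 8 to serve as the primary time point. Who takes up acupuncture is decided by the women themselves, after randomisation and in an unblinded trial. Splitting controls by uptake therefore does not restore a randomised comparison with usual care alone.

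Two things are at stake. A week-8 result could be read as evidence about usual care alone when it is not, and a lasting benefit could look smaller than it is. The and/or wording also leaves the primary time point open between a clean visit and a contaminated one.

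**Working it through.** **Inputs from Statistical methods and sample size:** difference 15.34, SD 26.5, power 90%, α 5%, allocation 2:1, withdrawal 20%, groups of 120 and 60. The sidedness of α is not stated; two-sided is used because it reproduces the plan's figure and one-sided does not (39 controls before withdrawal instead of 48).

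**Step 1. Reproduce the planned size.**
- Controls: n = (1 + 1/2) × [26.5 × (1.960 + 1.282) / 15.34]² = 47.04, rounded up to 48. Acupuncture: 2 × 48 = 96.
- Withdrawal: 48 / 0.80 = 60 and 96 / 0.80 = 120, total 180. This matches exactly.

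**Step 2. Power at week 4, before any deferred treatment.**
- SE = 26.5 × √(1/96 + 1/48) = 4.68, and 15.34 / 4.68 = 3.27.
- A two-sided 5% t-test on 142 degrees of freedom has power 90% (noncentral t; the normal approximation gives 90.6%).

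**Step 3. Week 8 with deferred treatment among controls.** Three assumptions are needed, none given in the article:
- a share c of controls takes up acupuncture;
- those controls gain the full effect by week 8;
- the acupuncture arm keeps its full effect four weeks after its last session.

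Expected difference = 15.34 × (1 − c), with the same SE:

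| Assumed uptake c | Expected difference | Power, 96 vs 48 |
|---|---|---|
| 0% | 15.34 | 90% |
| 10% | 13.8 | 83% |
| 25% | 11.5 | 68% |
| 50% | 7.7 | 37% |
| 75% | 3.8 | 13% |
| 100% | 0 | 5% (error rate only) |

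**Step 4. Relax the third assumption.** If the acupuncture arm keeps only a fraction r of its effect at week 8, the expected difference is 15.34 × (r − c). With r = 0.5 it is 15.34 × (0.5 − 0.5) = 0 at 50% uptake, and 15.34 × (0.5 − 1) = −7.7 at 100% uptake. The sign could therefore reverse while acupuncture works in both arms.

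**Step 5. Set the sections side by side.** The Abstract permits week 4, week 8 or both as primary. The statistical section ties its two-group test to the end of treatment only. Interventions makes week 4 the last visit at which the control arm is, by design, untreated with acupuncture. Only week 4 is consistent with all three.

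**The case against.** Deferred treatment for controls is an ordinary design choice, and the one two-group test with a stated time point is the clean one. Week 8 as an endpoint appears only in the Abstract, so part of the problem is a mismatch between Abstract and methods. Comparing the arms as randomised at week 8 is also still a valid randomised contrast if it is called what it is: immediate against optional deferred acupuncture. All of this stands, and it narrows the point.

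Three stronger readings are tempting but not supported:
- **That weeks 6 and 8 compare acupuncture with acupuncture.** Treatment of controls is elective and uptake is not given, so this would hold only at 100% uptake. Even then the arms would differ in timing.
- **That a contaminated week-6 group test is planned.** Table 2 shows data collection at week 6; no group test at that visit is stated.
- **That the repeated-measures trend test is contaminated.** Its visits are not named, and an article may leave that detail to the full protocol or SAP. It is affected only if weeks 6 and 8 enter the model.

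The objection does not remove the conflict. The article itself states both the offer to controls and week 8 as a possible primary time point in both groups. That is a contradiction in what is written, not a detail left to another document.

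**Conclusion.** The point holds for week 8 as a primary comparison. As written, the week-8 group difference would not estimate the effect against usual care alone, and the Abstract and the statistical section disagree on the primary time point.

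The loss depends on uptake. It is modest at 10% (power 83%), serious at 50% (37%) and complete at 100%. These figures illustrate the mechanism and are not a forecast. A benefit would appear to vanish altogether only at very high uptake, or at moderate uptake combined with a waning effect in the acupuncture arm.

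The week-4 contrast, its 90% power and the sample size of 180 need no change. For the trend test the concern is conditional on its visits.

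**What to change.** 1. Name the change from baseline to week 4 as the single primary endpoint, and make the Abstract and Statistical methods and sample size agree.
2. Limit between-group inference against usual care alone, including the repeated-measures analysis, to weeks 0–4, and name the visits in that analysis.
3. Report weeks 6 and 8 in one of two ways. The first is descriptive, within the originally treated arm, stating that this is uncontrolled and that the Background says vasomotor symptoms often resolve without treatment. The second is a comparison by randomised arm, explicitly labelled immediate against optional deferred acupuncture.
4. Record whether and when each control started acupuncture, if the case report form does not already do so, and show control data after week 4 by that status, descriptively.

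The offer of deferred treatment can stay as it is. The cost is wording and, at most, a small addition to the case report form. The real downside is that the trial makes no randomised claim against usual care alone after week 4.

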### Study outcome

The primary outcome measure is the hot flush score, produced by multiplying severity and frequency of hot flushes during a 24-hour period in a daily diary, which demonstrates validity and reliability in measuring hot flush activities [27]. Participants will be asked to record the number and severity of daily hot flushes during the entirety of the study period. Participants in both groups will also be routinely encouraged to fill out the diary by periodic short message service (SMS) and phone-call reminder both in order to avoid the selective loss to follow up, that is, selection bias and to prevent the indolence of writing daily diaries which are associated with participant knowledge-related bias in this unblinded trial. We will employ the slightly modified severity rating scale (0:none, 1:mild, 2:moderate, 3:severe, 4:very severe) suggested in the studies of Sloan et al. [27].

We will examine the reduction in hot flushes over a 24-hour period, as well as daytime and nighttime separately for sub-analytic purpose to check whether acupuncture has different effects on daytime versus nighttime hot flushes.

The secondary outcome measure is the Menopause Rating Scale (MRS) to assess other vasomotor symptoms. MRS is a highly qualified self-administered questionnaire for assessment of menopausal symptoms [37]. It contains 11 questions divided into 3 categories: psychological, somatic and urogenital.

We will also estimate the expectations of participants by using the credibility and expectancy questionnaire, aiming to determine whether expectations make a difference to outcome [38,39]. In order to assess expectations without potential influences by participants' knowledge of allocation results, a questionnaire will be administered to eligible women before notification of assignments. Data collection schedule is detailed in table 2.

**Table 2 T2:** Data Collection Schedule

Measures	Screening	Baseline Randomization				End		Follow-up
Week number	-1	0	1	2	3	4	6	8

Sociodemographic characteristics	O							
Hot flush diary	O	O	O	O	O	O	O	O
Credibility and Expectancy questionnaire		O						
MRS		O		O		O	O	O
Medical history	O							
Physical activity	O							
Smoking/Alcohol	O							
Pharmaceutical therapies (OTC and prescribed drugs)	O	O	O	O	O	O		O
Herb medications	O	O	O	O	O	O		O
Adverse effects			O	O	O	O		
FSH, Estradiol	O							
TSH, Free T4	O							

In case of an unblinded trial, the rater(or assessor) knowledge of treatment assignment could modify the outcome assessment [40]. We employed only patient- reported and self-administered outcomes with concerns of potential rater bias in outcome assessment. However, related bias due to the unblindness might still occur despite all of efforts to prevent them. It should be recognized as an unavoidable limitation of this study design.

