## Methods

### Inclusion criteria

Participants will be recruited from four centers (Seoul, Ilsan, Jecheon and Busan) by the use of local newspaper advertisements and posted notices at clinic cites. Participants include perimenopausal or postmenopausal women from 45 to 60 years old, who have average daily hot flush scores > 10 for one week prior to the screening visit (Hot flush scores: daily frequency × severity [0: none, 1: mild, 2: moderate, 3: severe, 4: very severe]). Serum TSH and free T4 levels will be tested to determine normal thyroid function.

We defined the term "perimenopausal" as menstrual irregularity or amenorrhea of 3–11 months [29,30], and the term "postmenopausal" as (1) 12 months of spontaneous amenorrhea or (2) 6 months of spontaneous amenorrhea with serum FSH levels > 40 mIU/ml or (3) 6 weeks postsurgical bilateral oophorectomy with or without hysterectomy or (4) hysterectomy with at least one intact ovary [31,32]. Despite the recommendation of the korpilampi workshop(1986) not to combine subjects undergoing natural menopause with those experiencing surgical menopause for analytic purposes [33], related studies which compare the risk of menopausal symptoms by the type of menopause are sparse and have shown conflicting results [34-36]. We thus included women undergoing menopause due to both natural causes and surgery. Instead, we will not only analyze data in a pooled population, but also perform a sub-analysis examining data separately for those with natural or surgical menopause.

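### The day-versus-night question is about a difference in treatment effects, but the plan gives it only separate daytime and nighttime analyses, which do not test that difference

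*Protocol article*

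**What the plan says.** All references are to the protocol article.

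- **Study outcome.** Besides the 24-hour score, reductions are to be examined "daytime and nighttime separately for sub-analytic purpose to check whether acupuncture has different effects on daytime versus nighttime hot flushes". Question and method stand in one sentence.
- **Exclusion criteria and Table 1.** Women who work at night are excluded so that day and night flushes can be analysed apart. The question therefore costs some eligibility.
- **Abstract, Discussion paragraph.** "Further analysis will examine the frequency, severity and difference in symptoms for daytime vs. nighttime hot flushes". This mentions a difference in symptoms between periods but names no comparison of treatment effects between periods.
- **Statistical methods and sample size.** Changes from baseline to end of treatment "will be compared using two-sample t-test or Wilcoxon rank sum test". In addition, "A trend test will also be performed using repeated measures analysis of variance", and there is adjustment for confounders. No treatment-by-period contrast or interaction is described.
- **Inclusion criteria.** Women with natural and with surgical menopause are both enrolled. The plan is to analyse them pooled and also to "perform a sub-analysis examining data separately for those with natural or surgical menopause". The text does not say that this split will be used to judge whether the effects differ.

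**The concern.** Two separate between-arm tests each ask whether acupuncture plus usual care differs from usual care alone within one period. Neither asks whether the daytime effect differs from the nighttime effect. If one p-value falls below 0.05 and the other does not, the natural reading is that acupuncture works in one period only. That pattern arises readily when the effects are identical, because each half-score is tested with less than the full trial's power and the two test statistics are only partly correlated.

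At stake is a false statement about when acupuncture works. This goes beyond a detail left for the statistical analysis plan: the article pairs this question with this method, and an analysis plan that followed it literally would inherit the mismatch.

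**Working it through.** **Inputs from Statistical methods and sample size.** The design is to "detect a hot flush score difference of 15.34 with a standard deviation of 26.5", with 90% power, α of 5%, 2:1 allocation, 20% withdrawal, and 120 and 60 participants. Sidedness is not stated; I take it as two-sided.

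**Step 1: reproduce the plan's own figure.** Controls needed = (1 + 1/2) × [26.5 × (1.960 + 1.282) / 15.34]² = 47.04, rounded up to 48, with 96 on acupuncture. Dividing by 0.8 gives 60 and 120, which matches. I use 48 and 96 evaluable women below.

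**Step 2: equal day and night effects.** Assumptions, none given in the article:
- the 24-hour score is the sum of a day part and a night part with equal SD;
- each part carries half the planned effect, 15.34 / 2 = 7.67;
- the two parts have correlation ρ within a woman.

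Then:
- SD per period = 26.5 / √(2 + 2ρ)
- SE per period = SD × √(1/48 + 1/96)
- power per period, P = Φ(7.67/SE − 1.96)
- P(both significant) from a bivariate normal with correlation ρ
- P(exactly one significant) = 2 × (P − P(both))

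| ρ | SD | SE | P | P(both) | Exactly one significant |
|---|---|---|---|---|---|
| 0.3 | 16.4 | 2.91 | 0.752 | 0.598 | 31% |
| 0.5 | 15.3 | 2.70 | 0.809 | 0.700 | 22% |
| 0.7 | 14.4 | 2.54 | 0.855 | 0.785 | 14% |
| 0.9 | 13.6 | 2.40 | 0.891 | 0.858 | 7% |

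If the true effect is 75% of the planned one, the last column is 40%, 33% and 24% at ρ of 0.3, 0.5 and 0.7.

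**Step 3: the direct contrast.** For each woman take the day change minus the night change and compare it between arms. Its SE is the per-period SE × √(2 − 2ρ). A two-sided 5% test on it errs 5% of the time when the effects are equal. The difference in effects detectable with 90% power is (1.960 + 1.282) × SE: 11.1, 8.8 and 6.4 points at ρ of 0.3, 0.5 and 0.7.

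**Step 4: menopause type.** The article gives no surgical share, so f is assumed. The SE of the difference in effects is 26.5 × √(1.5/(48f) + 1.5/(48(1 − f))). At f = 0.2 this is 26.5 × √(0.156 + 0.039) = 11.7, so the 95% CI half-width is 1.96 × 11.7 = 23 points. Power to detect a difference as large as the whole planned effect (15.34) is 16%, 26%, 32% and 37% at f of 10%, 20%, 30% and 50%.

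**The case against.** The best defence is that the article states no decision rule. It gives an aim and says the periods will be examined; it does not say that one significant and one non-significant result will count as a difference. The abstract's mention of a day/night difference leaves room for a contrast, and formal tests for sub-analyses often sit in the analysis plan. This stands in part. The percentages above describe what would follow from reading the separate p-values against each other, a rule the article invites but does not state. What survives is that the article fixes separate analyses as the means of checking for different effects and names no contrast anywhere.

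Four stronger readings are tempting and are not supported.

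- **That the separate analyses cannot answer the question at all.** Separate estimates can be contrasted. For menopause type the subgroups are independent, so two estimates and their standard errors suffice. For day and night the within-woman correlation is also needed, which the day-minus-night difference handles. The fault is that no such contrast is stated.
- **That menopause-type differences will be judged from separate p-values.** The Inclusion criteria section responds to a recommendation against combining the two types by adding separate analyses; it announces no comparison. With equal true effects, exactly one subgroup would be significant about 63% of the time at an assumed 20% surgical share. That figure applies only if someone reads the split as a comparison.
- **That false day/night differences will be frequent.** This depends on a correlation the article does not give; at 0.9 the rate is only 7%.
- **That day and night scores differ in level, so point reductions are not comparable.** The article gives no levels by period.

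**Conclusion.** The concern holds for day versus night: the stated method does not test the stated question. Under the trial's planning values the chance of a spurious one-period result runs from 31% at correlation 0.3 to 7% at 0.9, against 5% for a direct test. This rests on an equal split of effect and variance between periods, an assumed correlation, and conclusions drawn from separate p-values. For menopause type the point is conditional: it applies only if a difference is to be claimed, and the trial could say little about one. These are sub-analyses, so the primary conclusion is untouched; the change should be made but is not critical.

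**What to change.** 1. In Study outcome or the analysis plan, state that the day/night question will be answered by each woman's day-minus-night difference in change from baseline, compared between arms (equivalently, a treatment-by-period term), with a 95% CI and labelled exploratory.
2. State that no claim of different day and night effects will rest on separate p-values. The separate results can still be shown descriptively.
3. For menopause type, state that any claimed difference will be supported by the treatment-by-menopause-type interaction with its 95% CI, also exploratory. The term can go into whichever adjusted model is used.

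The points scale already planned is adequate. A log or percent-of-baseline scale changes what an equal effect means, and would be undefined for a woman whose nighttime baseline is zero.

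The cost is a few sentences and two extra estimates from diary data and menopause status already being collected. The downside is that the menopause-type interval will be wide (about ±23 points at a 20% surgical share) and its power low. The interval would show that limit openly.
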